## **6.2 Study Procedures**

Dispensing of sodium benzoate to participants will occur once consent has been obtained and after the screening phase and randomisation has occurred. A delegated Research Pharmacist at the Princess Alexandra Hospital will dispense medication for all sites. For each randomised participant, the entire 12 weeks of study medication will be provided to QCMHR delegated research staff. The study medication will then be distributed to the participant on a fortnightly basis by delegated research staff in line with this protocol (section 7.4). There will be a total of 6 dispensations per participant.

## **6.3 Study Restrictions**

There are no restrictions to participants during the study in terms of concomitant medications, exercise or ambulation. While sodium benzoate is often added to vitamin C rich products such as orange juice, there has been concern that sodium benzoate may interact with high dose vitamin C formulations to produce benzene (a known carcinogen). There is an absence of clear guidance on this matter, thus for the purposes of this protocol, we will adopt a conservative stance and require patients to avoid using vitamin C formulations that contain more than 500 mg/day (multivitamin tablets have lower doses of vitamin C and can be continued during the study, as can citrus fruits and food products that contain vitamin C naturally).

## **6.4 Safety Assessments**

All patients recruited in this study will be active cases at Queensland Hospital and Health services. The study team will liaise with clinical staff to ensure that participants have undergone a routine physical health screen.

Female participants will have a urinary pregnancy screen at baseline prior to inclusion, and during the study if indicated.

### **6.4.1 Adverse Events**

The Investigator and designated study personnel will monitor each participant for adverse events during the study. All adverse events reported between consent and final follow-up visit will be recorded in the case report form (CRF). The investigator or designee will ask the participant non-leading questions in an effort to detect adverse events e.g. "Have you felt unwell or different in any way since your last visit".

In addition, participants will be encouraged to spontaneously report any unusual feelings or sensations. See Section 8 for full details on adverse event reporting.

### **6.4.2 Other Safety Assessments**

If the participant is of child-bearing potential and sexually active, urine pregnancy tests will be conducted at baseline or when clinically appropriate.

### **6.4.3 Pharmacokinetics**

The following information is sourced directly from the Concise International Chemical Assessment Document 26 "Benzoic Acid and Sodium Benzoate", World Health Organization.

After oral ingestion of benzoic acid and sodium benzoate, there is a rapid absorption (of undissociated benzoic acid) from the gastrointestinal tract in experimental animals or humans. One hundred percent absorption can be assumed from the general literature when sodium benzoate is administered orally. In humans, the peak plasma concentration is reached within 1–2 hours. In the acid conditions of the stomach, the equilibrium moves to the undissociated benzoic acid molecule, which is believed to be absorbed rapidly. Benzoate from sodium benzoate changes from the ionized form to the undissociated benzoic acid molecule. As a result, the metabolism and systemic/toxic effects of benzoic acid and sodium benzoate can be evaluated together.

After oral and dermal uptake, sodium benzoate is metabolized in the liver by conjugation with glycine, resulting in the formation of hippuric acid. The rate of biotransformation in humans is high: after oral doses of 40, 80 or 160 mg sodium benzoate/kg body weight, the transformation to hippuric acid was independent of the dose — about 17–29 mg/kg body weight per hour, corresponding to about 500 mg/kg body weight per day. Other authors obtained higher values of 0.8–2 g/kg body weight per day. Hippuric acid is rapidly excreted in urine. In humans, after oral doses of up to 160 mg/kg body weight, 75–100% of the applied dose is excreted as hippuric acid within 6 hours after administration, and the rest within 2–3 days.

The limiting factor in the biosynthesis of hippuric acid is the availability of glycine. The utilization of glycine in the detoxification of benzoate results in a reduction in the glycine level of the body. Therefore, the ingestion of benzoic acid or its salts affects any body function or metabolic process in which glycine is involved; for example, it leads to a reduction in creatinine, glutamine, urea, and uric acid levels.

Another metabolite of benzoate is the benzoyl glucuronide. For example, the dog excretes considerable amounts of this metabolite in the urine (20% after a single dose of 50 mg/kg body weight). In healthy adults, up to 97% of the dose of sodium benzoate is excreted as hippuric acid in the urine within 6 hours

## 6.5 Pharmacodynamics

The desired pharmacodynamic outcome of sodium benzoate relates to its ability to inhibit D-amino-acid-oxidase (DAAO). DAAO is an enzyme that metabolizes D-amino-acids, such as D-serine and D-alanine. Sodium benzoate binds to the D-amino-acid-oxidase active site, which inhibits its ability to metabolize D-amino-acids. Consequently, by inhibiting DAAO, this results in increased concentrations D-amino acids. As D-serine and D-alanine are full agonists of the glycine binding site of the NMDA receptor, the increased cerebral concentrations of these D-amino acids result in increased NMDA function.

## 7 Investigational Product

### 7.1 Description of Investigational Product

Active: Sodium benzoate 500 mg per gelatine capsule administered at 1000mg per day (500mg BD)

Placebo: Microcrystalline cellulose in matched gelatine capsule

## 7.2 Dose Justification

With respect to the use of sodium benzoate as a food, the Joint Food and Agriculture Organization of the United Nations (FAO) / World Health Organization (WHO) Expert Committee on Food Additives, established a preliminary acceptable daily intake of up to 5mg/kg body weight for sodium benzoate. This translates to 350mg per day for a 70kg person.

With respect to individuals with urea cycle disorders, the recommended dose of sodium benzoate is between 250-500mg/kg per day or approximately 17500mg-35000mg per day for a 70kg person. It is noted that serious side effects at this dosage are rare and limited to occasional cases of anorexia and vomiting.

With respect to the use of sodium benzoate for the treatment of schizophrenia, we are guided by the dose used on Lane and colleagues (2013). In the main study the investigators also described a pilot study (n=7) dosing sodium benzoate between 250 and 1000mg/d. 1000 mg/d resulted in the largest decrease in psychotic symptomatology with no evident adverse reactions. In this patient group, a dose of 1000 mg per day was not associated with significantly more adverse events compared to placebo. Treatment-emergent adverse events included weight gain (n=1), insomnia (n=2), and tachycardia (n=1). It was noted that these adverse events were mild, brief and did not warrant medical treatment. The authors concluded these events were likely coincidental observations. Routine blood cell count, chemical analysis results and electrocardiogram after treatment remained unchanged and were all within normal ranges.

## 7.3 Comparator Justification

This study will use a placebo adjunct to routine care (routine care in this study is defined as 'individualized combinations of psychopharmacology, behavioural interventions, rehabilitation and associated clinical services in keeping with Queensland Health standards of care for psychosis') as a comparator condition. The Declaration of Helsinki affirms that placebo-controlled trials should only be used in the absence of existing proven therapy. Therefore the use of an adjunct therapy has been selected to ameliorate these ethical concerns as both the experimental and control groups will receive standard medical care (Treatment as Usual).

## 7.4 Administration

Sodium Benzoate – 1000mg (500mg BD with meals-reminder aid) capsules will be used in the study.

Placebo – identical-appearing microcrystalline cellulose gelatine capsules will be used in the study.

## 7.5 Randomisation Procedure

Participants will be randomised once written consent has been obtained and the baseline assessments have been completed. Participants will be randomised to one of the treatment groups, using blocks of 4 via a computer-generated randomization table. Randomisation will be stratified by five sites (a) Metro North HHS, (b) Metro South HHS, (c) West Moreton HHS, (d) Gold Coast HHS, and (e) Children's Health Queensland HHS. Participants will receive either active treatment or placebo in a 1:1 ratio.

The investigational products will be manufactured in accordance with current Good Manufacturing Practice (GMP) in a suitable TGA licensed facility. This same company (Pharmaceutical Packing Professionals) will hold the randomisation code, and provide a 24 hour

1800 number to unblind participants if required. Participants will be randomised strictly using a chronological process. Participants will be allocated a unique identification number which will be linked to the specific site number. If a participant withdraws from the study then the participant number will not be re-used nor will the participant be allowed to re-enter the study.

The randomisation will be double-blind. An independent Biostatistician will generate the randomisation list which will be provided to the manufacturer. The independent manufacturer will hold the closed randomisation list and be the only one who has the ability to unblind. In the case of emergency where it is crucial the medical staff knows whether the participant is on sodium benzoate or placebo, participants will be provided with contact information (i.e. 24 hour 1800 number) for unblinding.

## **7.6 Frequency of visits and follow up**

Participants will be clinically assessed at baseline, week 2, 4, 6, 8, 10 and 12. The study team will also contact participants once a week between face-to-face assessments by phone (if no phone then face to face assessment). Refer to Table 1 Schedule of Visits and Assessments.

## **7.7 Blinding and Unblinding Procedure**

All medication will be blinded to the study personnel, research pharmacist and the patient. Sodium benzoate and placebo capsules will be identical in packaging, appearance, colour and taste. Treatment allocations will not be disclosed to the Investigator or any study personnel before the database is locked, unless in the case of an emergency requiring unblinding. Unblinded participants will be withdrawn from the study.

Only in the event of a medical emergency which the investigator feels cannot be adequately managed without knowing the identity of the study medication, will the treatment code be unblinded for a particular participant. This will be done by the independent manufacturer via the 24 hour 1800 number. All cases of emergency unblinding will be documented on a Serious AE Form and reported to The University of Queensland, (Sponsor) within 24 hours.

After the completion of all participants in the study (last patient last visit), participants will be notified which arm of the study they took part in.

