## 8.8 Follow-up of AEs and SAEs

All AEs and SAEs documented at a previous visit/contact and are designated as ongoing, will be reviewed at subsequent visits/contacts.

All AEs and SAEs will be followed until resolution, until the condition stabilises, until the event is otherwise explained, or until the Participant is lost to follow-up. Once resolved, the appropriate AE/SAE Case report Form (CRF) page(s) will be updated.

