## 1029 **10 Case Report Form (CRF)**

1030 A Case Report Form (CRF) will be completed for each study participant summarising all clinical  
1031 screening and study data that is to be provided to the University of Queensland (Sponsor) for data  
1032 analysis. In the CRF, participants will only be identified by their participant number in order to  
1033 retain participant confidentiality.

1034

1035 The completed Case report Forms (CRF's) will be retained by the Investigators for a period of at  
1036 least 15 years or the maximum time frame as determined by local regulations, whichever is the  
1037 longest.

1038

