## **12 Data Management**

### **12.1 Documentation**

A screening log will be utilized to track potential participants and also record the counts of individuals approached, consented, meeting inclusion/exclusion criteria, withdrawals, and completion (in keeping with standard CONSORT diagram requirements).

The Case Report Form (CRF) will comprise of the hard copy questionnaires, clinical assessments and measures. These de-identified data will be retained in a secure room, in a locked filing cabinet, at each site.

De-identified data from the CRFs will be entered into REDCap, which is a secure (encrypted to health service standard, housed on a server behind the University of Queensland firewall), web-based application for building and managing online surveys and databases. Delegated research assistants will be trained in, and responsible for, entering data into the database.

Upon completion and resolution of monitoring and data management queries, the clinical trial database will be closed. All data will be exported into SAS software to enable statistical analysis.

A copy of the PICF will be stored in a secure room in a locked filing cabinet separate from the CRFs.

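### Section 7.7 ties telling participants their arm to last patient last visit rather than database lock, so it permits disclosure while study personnel should still be blinded

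*Protocol*

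**What the plan says.** Section 7.7 contains two timing rules. For staff: "Treatment allocations will not be disclosed to the Investigator or any study personnel before the database is locked", with one exception, "unless in the case of an emergency requiring unblinding". For participants, the rule takes effect after everyone has completed the study: "last patient last visit), participants will be notified which arm of the study they took part in". The second rule does not mention the lock, gives no latest date and does not say who does the notifying.

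Section 12.1 places the end of data handling later: "Upon completion and resolution of monitoring and data management queries, the clinical trial database will be closed". Section 8.8 allows safety work to run past the last visit: "All AEs and SAEs will be followed until resolution, until the condition stabilises".

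Two further statements bear on how the information would travel. Section 7.5 says "The independent manufacturer will hold the closed randomisation list and be the only one who has the ability to unblind". Section 10 says that in the case report form "participants will only be identified by their participant number".

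**The concern.** A double-blind trial protects its data until lock because judgement is still being exercised up to that point: on queries, on adverse-event assessments and on who is analysed. Section 7.7 accepts that principle for staff but releases participants from it at an earlier event. A participant who has been told their arm can pass it on to the person following up an adverse event, or to the clinical team with whom the study liaises. If study staff deliver the news themselves, they know the allocation directly. Either way, the blind of study personnel could end before lock even though everyone has followed the notification sentence as written.

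At stake is the credibility of the decisions that remain open between the last visit and lock. The efficacy ratings themselves will already have been made.

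**Working it through.** No sample size, power or error rate is involved, so there is nothing to recompute. The check is the order of events.

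**Milestones and their sources**

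| Step | Event | Source |
|---|---|---|
| 1 | Last scheduled efficacy ratings, including PANSS, at week 12 | Table 1; section 7.6 |
| 2 | Final visit at week 14, end of adverse-event recording | Section 8.3; Table 1 |
| 3 | Monitoring and data management queries resolved | Sections 12.1 and 13 |
| 4 | Database closed, read here as the lock of section 7.7 | Section 12.1 |
| 5 | Disclosure to the Investigator and study personnel allowed | Section 7.7 |

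For the last participant, step 2 is last patient last visit. Notification of participants is allowed at any time after step 2. Disclosure to staff is allowed only after step 4. The interval between steps 2 and 4 is where the two rules diverge. The protocol gives no length for it.

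**What can still change in that interval**

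- Queries. Under section 13, entry checks are made as data are entered, but a data manager later checks completeness and plausibility and settles the resulting queries with the study centre. These can concern PANSS records.
- Adverse events. Section 8.8 continues follow-up of events that are still open. Section 8.5 lets the causality assessment of a serious adverse event be amended when later data show it to be wrong. Sections 8.7.1 and 8.7.2 rest intensity and causality on the investigator's clinical judgement.
- Analysis sets. Section 16.13 makes participants who were treated outside the protocol, or who did not qualify for entry, ineligible for analysis. The rule is broad, its application needs judgement, and the section does not say when that judgement is made.

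**How disclosure to participants could reach staff**

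The manufacturer alone holds the code, and case report forms carry numbers only. Somebody must therefore link numbers to people before participants can be told. Study staff are the likely route, but that is an inference, since the protocol names no one. If staff are bypassed, the remaining route is a participant mentioning their arm during adverse-event follow-up, or through the liaison with the treating team described in section 8.11.

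**What cannot be affected**

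Every scheduled efficacy rating falls at step 1 or earlier, and notification cannot begin until every participant has finished. No scheduled PANSS rating can therefore be made by a rater who learned the arm through this provision.

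**The case against.** The strongest reply is that the two sentences are compatible. The notification rule says after, not at, last patient last visit, and so sets only an earliest point. The lock rule covers staff and the notification rule covers participants. Both are met if notification waits for lock. The rest of the protocol leans that way: if staff are to do the notifying, the lock rule already prevents them from receiving allocations sooner, and no direct route from manufacturer to participants is described beyond the emergency telephone number. The sentence can also be read as protective, since it stops anyone being told on finishing their own 12 weeks while others are still being treated.

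Most of this stands. A reader might infer that section 7.7 contradicts itself, or that it schedules disclosure before lock. The text supports neither. A reader might also infer that all 160 allocations would become known to staff. That is a bare maximum, which requires notification before lock and a leak from every participant, and the protocol gives no basis for either.

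The harm is also narrower than it may first appear. Ratings are complete, the later checks in section 13 are described as checks of completeness and plausibility and not as re-rating, and causality of a serious event is first assessed at the initial report. No routine contact is scheduled after week 14.

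The objection does not remove the gap. Compatibility depends on the notifier choosing to wait, and the only condition the protocol states for notifying participants is one that is met before lock. This is not a detail left for a later document: the protocol fixes the trigger itself, and at the earlier milestone.

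**Conclusion.** The point holds as a badly placed trigger. Literal compliance with the notification sentence permits participants to learn their arm before lock, and this could defeat the protocol's own rule that the Investigator and study personnel stay blinded until then.

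The exposure is limited to query resolution, open adverse-event follow-up, amendments to causality of serious adverse events, and exclusions under section 16.13. Its size cannot be quantified: the protocol gives neither the interval from last visit to lock nor the number of queries, events or exclusions likely to be open.

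The conclusion rests on two assumptions. The closing of the database in section 12.1 is taken to be the lock of section 7.7. It is also assumed that a notified participant, or whoever notifies them, could convey the arm to study personnel. The second is plausible but not stated.

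This is a cheap improvement to the protocol and does not threaten the primary outcome ratings.

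**What to change.** In the last paragraph of section 7.7, keep last patient last visit as a condition for notifying participants and add, directly after it, that the database must also have been locked. That is enough to align the sentence with the rule for staff earlier in the section. It would help to state in the same place who notifies participants, since the protocol is silent on this.

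The cost is one phrase and a somewhat longer wait before participants learn their arm. No visit, assessment or analysis changes. Emergency unblinding is untouched, because section 7.7 already treats it as a separate exception.

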## **7.8 Product Labelling**

The labelling of study medication will comply with local regulatory GCP and TGA requirements and medication dispensing guidelines.

## **7.9 Handling and Storage of Study Drugs**

Prior to dispensing, all study medication will be kept securely locked, in a dry, restricted access location at room temperature (20-25°C). Only delegated members of the study team will have access to the investigational products.

## **7.10 Accountability**

The designated Research Pharmacist will dispense study medication into the care of the delegated research staff, who will then sign that he/she has received the study medication for the study. The study drug will be kept in a securely locked area and provided to the participants according to the protocol (section 7.4). Participants will be requested to return all unused study medication (i.e.

unopened blister packs or capsules not taken) and empty blister packs to the delegated research assistants. All unused supplies of study medication will be accounted for and documented by the designated Research Pharmacist. Compliance with study medication will be calculated at each visit by means of self-report and a capsule count. This data will be used to calculate compliance with medication for analysis purposes. To further aid compliance and as a quick visual guide, participants will be offered a diary to document the date and time of scheduled visits and tasks to be undertaken.

All material supplied is for use only in this clinical study and should not be used for any other purpose. The Investigator is responsible for investigational product accountability, reconciliation and record maintenance. In accordance with all applicable regulatory requirements, the Investigator or designated site staff will maintain investigational product accountability records throughout the course of the study. These persons will document the amount of investigational product received from the Sponsor, the amount supplied and/or administered to and returned by participants, if applicable.

An investigational product dispensing Log will be kept current and will contain the following information:

- the identification of the participant to whom the drug was dispensed;
- the date(s) and quantity of the drug dispensed to the participant.

The inventory will be available for inspection by study monitors during the study. Drug supplies including participant returns will be collected at the end of the study by the study monitor, returned by the Investigator or designee to the Sponsor or authorised for destruction. When requested in writing by the Sponsor, unused drug supplies may be destroyed by the Investigator or delegate provided such disposition does not expose humans to risks from the drug. Records will be maintained by the Investigator of any such alternate disposition of the investigational product. These records will show the identification and quantity of each unit disposed of, the method of destruction (taking into account the requirements of local law), and the person who disposed of the investigational product. Where investigational product is destroyed on-site, a record of destruction will be issued. Such records will be submitted to the Sponsor for reconciliation purposes.

